
##### Concurrent EEG-QST measures]

EEG measures will be recorded using a portable, adaptable, and simple-to-use MENTALAB Explore + recording system developed and adapted to clinical use (Mentalab GmbH, Munich, Germany). EEG signals will be acquired by 32 electrodes mounted in an elastic cap and arranged according to the international 10–20 system. The EEG signal will be amplified and digitized using a sampling rate of 250 Hz, and the reference will be placed at CPz. Impedances will be kept under 10kΩ for all electrodes.

Firstly, resting state electroencephalography (rsEEG) will be recorded for 5 min with participants maintaining their eyes closed. The participant will be instructed to sit comfortably and relax letting their mind wander. Next, a second rsEEG recording will be performed, but with a cold noxious stimulus being applied to the palm of the dominant hand. At the end of the test, the participant will be asked to report the average level of pain perceived during the 5 min. The intensity of the cold pain stimulus must be between 3 and 5/10 on the NRS during the whole recording. The timeline for the concurrent measures is also illustrated in Fig. 1.

Finally, we will record Contact Heat Evoked Potentials (CHEPs) using concurrent QST-EEG.

CHEPs, mediated by Aδ fibers, are a neural correlate of nociceptive processing and dysfunction in humans [44, 97, 98]. CHEP parameters can inform researchers about the maladaptive neuroplastic changes in chronic pain patients, though this is not yet characterized in cancer patients [99]. We will apply 25 stimuli at 60 °C with a duration of 0.3 s and ramp-up and -down of 170 °C/sec, with an inter-stimulus interval of 10 s, to minimize saliency and startle responses. EEG will be simultaneously recorded. The baseline temperature will be 32 °C. If the stimulus is very painful, the temperature will be reduced by −1 °C. This process can be repeated until 55 °C is reached. At the end of the test, the participant will rate how painful the stimuli sequence was on average. The heat stimulation will be applied to the dominant volar forearm. The stimulation site will be moved slightly between each stimulus application to avoid habituation of the thermal receptors.

Amplitudes of the N1-P1 complex, N2, and P2 components during hot pain stimulation as well as time-frequency analysis of the EEG signals will be the focus of data processing. Quantitative EEG analytical techniques will enable the evaluation of changes in spectral power, coherence, and phase connectivity.

For the different QST stimulations, if the dominant volar forearm and palm are primary pain sites, the procedure should be applied to the non-dominant arm counterparts. If this is also considered a primary site of pain, the dorsum of the dominant forearm or hand will be used instead.

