#### Visit 4. Post-treatment assessment (Study site; T1).

The investigator will interview the patients to assess medication intake, receipt of any non-pharmacological treatment, and number of hours slept in the 24 h prior to the visit. The battery of questionnaires for patients and caregivers as well as the QST and EEG measures for the patients will be conducted, as in Visit 2. Again, the patients will be asked to fill in NRS of the primary and secondary endpoints during 15 days after the treatment. Patients will also fill in the questionnaire on cognitive complaints as in the pre-treatment and report global ratings of improvement and satisfaction with the home-based tES intervention.

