#### Visit 5. Three-month follow-up (Study site; T2)

The same procedure as in Visit 4, including QST and EEG assessments will be conducted three-months following the tES intervention. Caregivers will fill in their respective set of questionnaires. The socio-economic questionnaire will also be administered to both patients and relatives/caregivers. Again, we will ask the participants to fill in NRS of the primary and secondary endpoints during 15 days in this follow-up period.

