### Specific aims and hypotheses

This multicenter study will address many aspects of cancer-related persistent pain including its potential treatment with repeated tES and assessment of the effectiveness of the therapy using self-reported assessment of different symptoms of the disease, psychophysical testing using QST and neurophysiological testing using EEG. The aims and hypotheses of the study are as follows:Aim 1: To determine the therapeutic effects of 15-day home-based anodal tDCS and tACS interventions (compared to sham stimulation) on pain intensity (primary outcome), other dimensions of pain (pain unpleasantness, catastrophizing, interference), quality of life, cancer-associated symptoms (fatigue, depression, anxiety, sleep fragmentation, cognitive impairment), and global functioning among patients with cancer-related persistent pain. We hypothesize that compared to sham, tDCS and tACS will reduce clinical pain and associated symptoms as well as improve quality of life and global functioning. We expect that anodal tDCS might have a stronger effect on pain intensity, while tACS can have a stronger effect of decreasing stress, emotional processing of pain and improving quality of life. We will also test the feasibility of the home-administered tES (analyzing dropout rates, satisfaction scores, adverse and side-effects…). The potential long-term benefits of the interventions will also be addressed at three and six months post-treatment follow-ups.Aim 2: To identify psychophysical and neurophysiological predictors and mediators of tES-induced analgesia in patients with cancer pain. We hypothesize that the improvement in clinical pain will be mediated by intervention-induced adaptive changes in (i) nociceptive and pain modulatory system using QST indices and through contact heat-evoked potentials (CHEPs) using concurrent heat painful stimuli and EEG, as well as (ii) in oscillatory activity measured by resting state EEG.Aim 3: To identify responders to the tES interventions based on clinically relevant reduction in pain intensity (≥ 30%) and to characterize them according to central pain biomarkers using QST, EEG measures and/or sociodemographic, climical and disease related data. We hypothesize that indices of pain modulation and perception will be sensitive to predict treatment outcomes.

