**Fig. 1 Fig1:**
[figure not shown]
Timeline for each assessment visit including measures of quantitative sensory testing and electroencephalography. TSP, Temporal Summation of Pain; CPM, Conditioned Pain Modulation; HPT, Heat Pain Threshold; CDT, Cold Detection Threshold; CPT, Cold Pain Threshold; OA, Offset Analgesia; EEG, electroencephalography; rsEEG, resting state EEG; CHEP, Contact Heat Evoked Potential

FamiliarizationParticipants undergo a short training to familiarize themselves with the heat stimuli.
aHeat pain: 1 stimulus of 45 °C for 5s. Ramp-up and ramp-down: 170°C/s.bCold pain: 1 stimulus of 0 °C for 5s. Ramp-up and ramp-down: 170°C/s.

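### The heat level for the evoked potentials is not tied to the T0 level, so the stimulus can differ between a patient's visits with that day's pain sensitivity, which the treatment may change

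*Protocol article*

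**What the plan says.** The section on concurrent EEG-QST measures sets the stimulus: "We will apply 25 stimuli at 60 °C with a duration of 0.3 s". It then gives the tolerability rule, "If the stimulus is very painful, the temperature will be reduced by" 1 °C, with the limit "This process can be repeated until 55 °C is reached". The baseline temperature is 32 °C. After the sequence the patient gives one average pain rating. The trigger for a step down is the patient finding the stimulus very painful, and no rating cut-off is attached to it.

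Later visits repeat the procedure. For T1 the questionnaires "as well as the QST and EEG measures for the patients will be conducted, as in Visit 2". For T2, "The same procedure as in Visit 4, including QST and EEG assessments will be conducted three-months following the tES intervention". The caption of Fig. 1 gives a single sequence: "Timeline for each assessment visit including measures of quantitative sensory testing and electroencephalography".

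On use of the data, the same section names "Amplitudes of the N1-P1 complex, N2, and P2 components during hot pain stimulation", with time-frequency analysis, as the focus of processing. Aim 2, under Specific aims and hypotheses, expects pain relief to be mediated by adaptive changes that the intervention induces in the nociceptive and modulatory system, measured by QST indices and "through contact heat-evoked potentials (CHEPs) using concurrent heat painful stimuli and EEG". The statistical analysis plan section compares EEG measures by group and time. Its covariates are age, sex and cancer characteristics.

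**The concern.** An evoked-potential amplitude can be compared between visits only if the stimulus is the same or its difference is accounted for. Here the stimulus level is set by the patient's pain response, and at T1 and T2 that response comes after randomisation. It is also close to what the trial expects stimulation to change. If active treatment lowers heat sensitivity, patients who were stepped down at T0 will tend to receive a hotter stimulus afterwards, and this will happen more in the active arms than in sham. Randomisation does not balance a difference that treatment itself creates.

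The CHEP part of Aim 2 is at stake: the group-by-time comparison of amplitudes and the mediation hypothesis built on it. A small or absent CHEP change could mean no effect on nociceptive processing, or an effect partly offset by a stronger stimulus. The end-of-test pain rating has the same weakness.

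The other evoked measures are better protected. Temporal summation, conditioned pain modulation and offset analgesia use an individually determined temperature, and their indices are normalised differences within the visit. No comparable safeguard is described for CHEPs.

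**Working it through.** The article gives no sample size, power or effect figure for CHEPs, so there is no planned figure to reproduce. The check has three parts.

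**1. Reading the sections together.**
- The CHEP text gives one starting level (60 °C), one step (1 °C), one floor (55 °C) and a pain-based trigger. No individual level is carried between visits.
- T1 is conducted as T0, and T2 as T1. The figure caption gives one sequence for all assessment visits.
- Allocation follows Visit 2 (T0). The T0 level is therefore fixed before randomisation, and the T1 and T2 levels are not.

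Followed as written, each visit starts at 60 °C and steps down on that visit's pain.

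**2. Bound on the stimulus difference.**
- Possible levels: 55, 56, 57, 58, 59 and 60 °C, which is six levels.
- Largest difference between two visits: 60 − 55 = 5 °C.
- Step from baseline at the full level: 60 − 32 = 28 °C.
- Ratio: 5 / 28 = 17.9%.

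This is the extreme that the rule allows, not a typical value.

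**3. Illustration of attenuation.** All of the following are assumptions, because the article gives neither the share of patients stepped down nor the amplitude change per degree.
- The temperature at which a patient finds the stimulus very painful (the threshold) is Normal with mean μ and SD 2.5 °C.
- Delivered level = the highest whole degree not above the threshold, bounded to 55–60 °C.
- Response is proportional to (delivered level − threshold).
- Analgesia raises the threshold by d = 1 or 2 °C. At a fixed stimulus the true change is then −d.
- Observed change = (level at T1 − level at T0) − d, so masked share = mean(level at T1 − level at T0) / d.

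Three patients with d = 1 show the mechanism:
- Threshold 57.4 °C: level 57 at T0 and 58 at T1. Observed change = 1 − 1 = 0, so the effect is fully masked.
- Threshold 61 °C: level 60 at both visits. Observed change = −1, unaffected.
- Threshold 53.5 °C: level 55 at both visits. Observed change = −1, unaffected.

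Results from 200,000 simulated patients per row:

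| μ (°C) | Stepped down at T0 | Masked share, d = 1 | Masked share, d = 2 |
|---|---|---|---|
| 64 | 5–6% | 5% | 4% |
| 62 | 21% | 21% | 16% |
| 60 | 50% | 48% | 41% |
| 58.5 | 72–73% | 65% | 59% |
| 57 | 88–89% | 67% | 67% |
| 56 | 94–95% | 60% | 64% |
| 54 | 99% | 33% | 41% |

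The share falls in the last rows because many patients then sit at the 55 °C floor at both visits. With the T0 level held at T1 the masked share is 0 by construction. The share never exceeds 100% in this model, so it shows attenuation and no change of sign.

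**The case against.** The strongest reply has five parts.

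- **The restart is inferred.** No single sentence says that each visit begins again at 60 °C, and a condensed article may leave per-visit operating detail to a manual that is not shown. This stands as a limit on certainty. However, the article itself states the starting level, step and floor and says that later visits repeat the earlier ones. The point concerns a stated rule, and nothing in the article contradicts the reading.
- **The direction is not given.** Aim 2 speaks of adaptive changes without saying that CHEP amplitude should fall. This stands. If the adaptive change were a rise, a hotter stimulus would inflate it. Attenuation is therefore conditional; the mixing of stimulus and treatment effect is not.
- **Few patients may be affected.** The step is a tolerability cap. Patients who tolerate 60 °C at both visits, or are at 55 °C at both, receive the same stimulus. This stands, and the share is unknown.
- **Analysis can handle it.** Handling of delivered temperature may sit in an analysis plan that is not shown, and the stored QST and EEG device files may already hold the levels. The absence of a covariate is therefore not itself a fault. But adjustment cannot fully repair the problem, because the delivered level after T0 is affected by treatment.
- **The endpoint is secondary.** Daily pain ratings are untouched, and Aim 2 also uses QST indices and resting EEG. This limits the importance.

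A reader might also infer that a true benefit could come out reversed, or that the outcome is fixed as an unnormalised amplitude. The documents support neither. The illustration shows attenuation only, and the article names amplitudes without saying whether they will be normalised.

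**Conclusion.** The concern holds in a limited form. As written, the CHEP stimulus can differ between a patient's visits by up to 5 °C, according to a pain response that is post-randomisation at T1 and T2 and that treatment may change. For patients whose level differs between visits, the change in amplitude and in the end-of-test rating does not isolate the treatment effect.

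If treatment lowers both heat sensitivity and CHEP amplitude, the effect is attenuated. Under the assumptions above the loss runs from about 4% to 67% of the true change, driven mainly by the share stepped down at T0, which the article does not give. The result rests on reading the repeated procedure as a fresh start at each visit. It should not be read as showing that CHEP effects will be hidden in most patients. The primary outcome is not affected. The change is worth making because it is cheap and because a null CHEP mediation result would otherwise be hard to interpret.

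**What to change.** In the section on concurrent EEG-QST measures:

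1. State that the final level each patient reaches at T0 is the starting level at T1 and T2. Keep the existing downward tolerability step unchanged.
2. Log the delivered temperature of each of the 25 stimuli at every visit.
3. Base the T0 amplitude on stimuli given at that final level, because the text does not say whether stepping down happens before or during the sequence.
4. Keep all patients in the main CHEP analysis. Use restriction to visits with matched levels, or adjustment for delivered temperature, only as sensitivity analyses: both condition on a post-randomisation variable, and restriction could remove patients unequally between arms.

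The cost is about one line in the procedure and one recorded field, if the device files do not already hold it. Two small downsides remain. Visits at which the T0 level is no longer tolerated will still differ. If stepping happens during the sequence, some T0 averages will rest on fewer than 25 stimuli. For patients already assessed, the delivered levels should be recovered from the stored files where possible.

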## Data management and analysis

### Online data management system

The clinical data of the patients will be collected in the web-based PAINLESS platform, which was developed by Software Imaging & Vision information technology company (SIMAVI, Bucharest, Romania). The PAINLESS system is maintained on the infrastructure of the Supercomputing Centre of Galicia along with the associated collected data.

Patient data will be treated as strictly confidential, and the data collection will be pseudo-anonymized, protecting the participants’ identity. For this purpose, the study doctor will assign a unique code called the “Painless ID” to the participant with which they will be identified during all subsequent phases of the study. The data relevant to the study, except for patients’ names, will be recorded, processed, and stored together with this unique code identifier and all the clinical data related to the state of health. The profile data of the patient is stored in a different repository to the clinical data in order to create another layer of security. Only the physician and authorized parties will be able to link this code to the patients’ real identity. The only stored personal data relevant to the study are age and sex and does not identify the patient.

The system automatizes a lot of the processes related to the study. The registration process is automatized through the PAINLESS Platform. There is an Eligibility Questionnaire where the clinician enters the Painless ID and the answers the patient gave to some questions that are important to determine if the patient is eligible to participate in the project. The system then compares the answers to the eligibility criteria determined by the consortium and returns an Eligibility Code only if the patient is declared eligible. The patient can then use the Eligibility Code to register through the platform and will receive an email that they have successfully registered to the Painless Platform. A similar process is performed for caregivers, a caregiver code is generated associated with an existing patient and can be used code to register in the platform. Password recovery can also be done through email. The registration process has multiple steps in order to ensure the Painless Platform is a closed ecosystem and only selected personnel and patients have access for security purposes.

Patients, caregivers and clinicians can complete questionnaires about the state of health of the patients. The questionnaires become unlocked in the platform at different times based on the decisions of the clinicians. After a questionnaire is submitted, the responses are stored in the database of the project along with some calculated scores in the case of some questionnaires. The clinician is able to see how a patient answered their questions on the platform.

Another useful functionality of the PAINLESS platform is the ability to store medical files generated during the PAINLESS project. The project works with 3 different device types that generate files and the files can be saved, stored, visualized, downloaded, and validated through the platform. Some of the data are accessible to clinicians to visualize but some information is is able to be seen only available if to a person designated as administrator in each organization downloads the full file. This is done in order to protect the integrity of the research since most clinicians should not be informed if the patient has received a real tES stimulation or a sham. For QST and EEG, MentaLab type data, the process is the same to provide consistency to the platform.

The patient data are subject to medical confidentiality and the provisions of the General Data Protection Regulation of the European Union. Only information that cannot be identified can be passed on to other members of the consortium. The data will be kept pseudo-anonymized at the end of the study, with the destruction of the code identity relationship for future use, subject to express permission being sought and provided that the participants agree to it. The data will be stored for 15 years and then deleted. Participants have the right to access, to rectify, to erasure, to data portability, to be notified, to object, and the right regarding automated individual decision-making, including profiling.

All the data collected in the PAINLESS project will be used to train artificial intelligence models, but no personal data will be used. The models will have two primary functions: to improve knowledge about palliative care for patients and to increase the standards of care for cancer patients. The patients are informed prior to registering that their data will be used for artificial intelligence, and they must consent for their data to be used. To preserve human agency, the system will not transmit recommendations directly to the patients, all such recommendations will first be checked by a medical professional to ensure their validity.

### Sample size calculation

To calculate the sample size, we considered the data of a recent meta-analysis of 13 studies with data originating from 398 participants with chronic pain. Active tDCS has been reported to have a superior effect than sham with a medium-large size effect (standardized mean difference= −0.76 +/– CI 95% = −1.24) [100]. However, the effect size of tDCS varied considerably between studies, for which reason we decided to achieve small effect sizes to ensure the robustness of our results. Thus, we used G*Power software (Version 3.1.9.7) to calculate the sample size sufficient to reach a small effect size (f = 0.095) with mixed model analysis of variances (ANOVA), setting alpha at 0.05 and power (1-β) at 0.9. The sample was estimated as 291 participants. Thus, we will recruit 450 participants to compensate for eventual dropouts or attrition during the treatment or at the follow-ups (approximately 30%).

### Statistical analysis plan

The statistical plan was accepted by the ethical committees of the involved centers. To ensure that the treatment groups (tDCS, tACS, sham) were comparable, we will perform a one-way analysis of variance (ANOVA) for age, gender, clinical outcomes and a chi-squared analysis for the demographic variables, medication pattern, and the rest of categorical variables.

 Aim 1 and 2: We will implement an intention-to-treat analysis approach, including all randomized participants who received at least 10 consecutive stimulations [101, 102]. Missing data will be imputed following the method that allowed us to obtain the best adjustment. We will address our primary and secondary hypotheses using two complementary statistical approaches (Classical Frequentist and Bayesian statistics) to enhance the robustness of our findings (similar to Samartin-Veiga et al., 2022), as well as time series analysis. We will calculate mixed model ANOVAs for each outcome (scores of self-report questionnaires for both patients and care providers, as detailed in Sect. 4.2; QST and EEG measures) with the intervention group (tDCS, tACS, sham) as a between-subject factor and time (T0, T1, T2, T3) as a within-subject factor. Age, sex, and cancer characteristics (i.e., type extension, evolution, previous treatments) will be included as covariate variables in the statistical analysis. In the presence of statistically significant main effects and group*time interaction effects, Bonferroni-Holm corrected post hoc analyses will be conducted for multiple comparisons. The effect size will be computed as eta squared η2 and interpreted based on Cohen’s benchmark categorization (small, η2 = 0.01; medium, η2 = 0.06 and large, η2 = 0.14) [103]. The normality of residuals will be tested using Shapiro Wilk’s test and normality plots. The homoscedasticity assumption for mixed model ANOVA will be tested with the Levene’s test and the sphericity will be tested using the Mauchly’s test for repeated factors. In case of sphericity deviation, Greenhouse-Geisser corrections will be used.

Aim 3: Patients will be classified as *responders* to the intervention if they report a mean reduction in NRS pain intensity of at least 30% at T1 compared to T0. To characterize the best responders to tES, we will also use the algorithms developed in the precursor study to profile patients using the sociodemographic and clinical variables and biomarkers studied. We will conduct tree-based methods (linear mixed-effects model trees or, in broader terms, generalized linear mixed-effects model trees), which provide a convenient way of visualizing decision rules for predicting an outcome. Personalized treatment methods will be determined by using a convenient categorical tree-based algorithm.

Statistical significance will be set at *p* < 0.05.

